#### Plantarflexor force-matching the task

A force-matching task (FM) will be performed following the MVIC/RFD task in an identical position. Participants will be asked to maintain an ankle plantarflexor force equivalent to 10% of MVIC with visual feedback, a line indicating the target force, on a screen 1.5 m in front of them. Participants will be instructed to gradually reach the required force level and maintain this force for 15 s [25]. This force-matching task results in fluctuation around the target output, with smaller fluctuation indicating better muscle force control.

#### Test re-test reliability

A total of twelve healthy adult volunteers (seven males and five females, with a mean ± SD age of 37 ± 4.9 years, height 175 ± 10.8 cm, mass 65 ± 14.4.2 kg, BMI 21.1 ± 2.5) were recruited prior to the commencement of the study. Test-retest intra-rater reliability of diagnostic ultrasound imaging and the MVIC/RFD measures were determined across two sessions, 5 to 7 days apart. All measurements tested were on the right leg of the participants, and all demonstrated excellent reliability (ICCs >0.80 (95% confidence intervals 0.83 to 0.98) [26].

#### Plantarflexor six repetition maximum

Six repetition maximum (RM) of the seated and standing calf raise will be assessed bilaterally in random order, with 10 min rest in between. Repetition maximum is an accepted and reliable assessment of muscle strength [27]. Participants perform sets of six repetitions until a point of failure, establishing the maximum load for this number of repetitions; this commences at 80% bodyweight for seated exercises and 10% bodyweight for standing. Calf raise exercises will be standardised in terms of tempo, the height of the heel lift, the orientation of the tested foot, and upright trunk posture for standing exercises. For low-intensity groups, the baseline eighteen RM load will be estimated from six RM using the following formula: 6RM × 0.65 [28]. Week 1 exercise intensity will be adjusted down by 10% in both groups to minimise muscle soreness.

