**Fig. 2 Fig2:**
[figure not shown]
Calf raises in a Smith machine. A1) Starting position; A2) Ending position from standing; B1) Starting position; B2) Ending position from seated

The study groups will vary in terms of load intensity and time-under-tension (Table 1). Four sets of each exercise will be performed three times per week for 12 weeks, with standardised rest times. Participants will be taught to perform the calf exercise with appropriate fidelity, including a full available range of plantar flexion and dorsiflexion, performing the movement in the sagittal plane, smoothly and with appropriate tempo. Exercises will be externally paced with a metronome (an application downloaded to participants’ phones) to ensure that participants achieve the target exercise tempo.

**Table 1 Tab1:** Calf exercise dosage for each group. RM repetition maximum; TUT time-under-tension; DF dorsiflexion; PF plantarflexion; min minutes; S seconds

	Group 1 High intensity with high time-under-tension	Group 2 High intensity with low time-under-tension	Group 3 Low intensity with high time-under-tension	Group 4 Low intensity with low time-under-tension
**Load intensity**	6 RM	6 RM	18 RM	18 RM
**Repetition**	6	6	18	18
**Sets**	4	4	4	4
**Frequency**	3×/week	3×/week	3×/week	3×/week
**Duration**	12 weeks	12 weeks	12 weeks	12 weeks
**Contraction time/rep**	3 s concentric 3 s eccentric	1 s concentric 1 s eccentric	3 s concentric 3 s eccentric	1 s concentric 1 s eccentric
**Rest in between reps**	No	No	No	No
**Rest in between sets**	2 min	2 min	2 min	2 min
**Contraction time per set**	36 s	12 s	108 s	36 s
**Total contraction time**	288 s	96 s	864 s	288 s
**Total loading time in session (with rests)**	16 min and 48 s	13 min and 36 s	19 min and 12 s	16 min and 48 s
**Volitional muscular failure**	Yes	Yes	Yes	Yes
**Range of motion**	0° to 15° DF 0° to 50° PF	0° to 15° DF 0° to 50° PF	0° to 15° DF 0° to 50° PF	0° to 15° DF 0° to 50° PF
**Time between sessions**	48 h	48 h	48 h	48 h
**Exercise form**	Seated and standing calf raising both performed on a Smith machine with barefoot	Seated and standing calf raising both performed on a Smith machine with barefoot	Seated and standing calf raising both performed on a Smith machine with barefoot	Seated and standing calf raising both performed on a Smith machine with barefoot

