Exercise load progression will be monitored weekly based on the participant’s pain and ability. The load will be based on the volitional muscular failure, where failure is defined as an inability to do another full repetition. The load will be influenced by the self-reported pain during the exercise, with less than five on an eleven-point numerical rating scale (where zero is no pain and ten is the worst pain imaginable) being defined as acceptable [29]. For participants who report their pain as a five or more during the exercise, the load will be reduced so that pain severity is within an acceptable range. If the pain is still not acceptable with minimal load, bodyweight in standing and unloaded in seated, the exercise will be performed on flat ground. Participants continuing to experience unacceptable pain will commence with isometric exercise. As the dorsiflexed position is likely to be pain provocative due to greater Achilles tendon load, these will be performed with the ankle in a unilateral mid-range plantarflexed position, or bilateral if too painful. Initially, participants will perform five sets of 45 s at the highest load tolerable, based on pain and ability to complete the exercise, until isotonic exercise can be performed with acceptable pain response as assessed on a weekly basis (Fig. 3).

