### Primary feasibility outcomes: study processes

The following outcomes will be used to determine the feasibility of study processes for a randomised trial:
(i)Conversion, recruitment and retention rates. Conversation rate is the proportion of participants providing consent of those who met the selection criteria. Recruitment is the number of participants recruited per month. Retention is the proportion of recruited participants who complete the 12-week outcome assessment (primary endpoints).(ii)Exercise adherence and fidelity. Exercise adherence and fidelity will be assessed from the information recorded by physiotherapists at weekly videoconference sessions. Adherence to exercise will be expressed as the percentage of prescribed exercise sessions completed or attempted per week. Exercise fidelity will be expressed as the percentage of the following key dose parameters: appropriate tempo per contraction, volume [repetitions and sets], intensity [failure +/−1 repetition].(iii)Adverse events. The frequency (number of participants and number of cases), nature (e.g. rolled ankle, muscle tear or tendon pain worsening) and severity (mild, moderate or severe) will be recorded at each weekly videoconference session. People experiencing adverse events will be managed by the research team or triaged to an appropriate medical facility. The frequency of the use of paracetamol medication and other co-interventions to relieve Achilles pain will be also recorded.(iv)Feasibility to collect economic outcomes. This will inform the decision to use an economic evaluation in a future definitive randomised trial. Health-related work productivity [33], as well as health-care use—namely current medications and treatment for Achilles—will be assessed at weekly intervals via a questionnaire during videoconference sessions.(v)Participants’ and telerehabilitation care providers’ experiences with the interventions. At the end of the intervention period, two to three participants from each group will be invited to share their experience—the acceptability of interventions, and barriers and enablers to adherence—via qualitative interviews that will last for approximately thirty minutes. A focus group will be used to assess the views of videoconference care providers.

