### Data management and analysis

Both feasibility and clinical outcome data will be transferred to Excel spreadsheets, which will then be combined into one database. Quality checking for data entry will be performed by visually inspecting data and creating frequency tables for all items by two members of the research team. All data will be de-identified with analyses performed by an independent analyst. The randomisation code will not be broken until the final follow-up measurement has been performed (i.e. participant’s last visit), and data analysis has been completed. Both hard and soft copy data will be protected and accessible only to the research team. The principal investigator will have access to the final datasets. Results will be made available to participants on request and will be published in a peer-reviewed journal.

Means and standard deviations (or medians and IQRs, where data is not normally distributed), mean or median differences and their 95% confidence intervals of all outcome measures will be calculated at each follow-up time. Point estimates of effect will be calculated as the difference between group means expressed as a proportion of the pooled standard deviation. The effect size criteria will be interpreted as per Hopkins [45], with very large being ≥1.2, moderate being ≥0.6, and small being ≥0.2. Standard tests to assess continuous data for normal distribution will be used and transformation will be carried out if required for further analysis.

The MVIC force data (Nm) will be analysed directly from PowerLab (AD Instruments Corp, Dunedin, NZ) for each recorded trial. RFD data (N·s-1) and force match data will be exported to Excel (Microsoft Corporation, Redmond, WA). The RFD will be analysed using a custom-written software program (rehabtools.org, Sunshine Coast, Australia). For the FM task, a sample of force (from five to fifteen seconds during each trial) will be obtained to calculate the mean and coefficient of variation (CV) of force (SD/mean force % 100).

The trial will be deemed a success based on the following:
(i)Randomising 20% or more of eligible patients that fit the selection criteria.(ii)Achieving 66% or more of the number of sessions completed in each group.(iii)Achieving 66% or more of intervention fidelity (i.e. prescribed dose parameters including tempo, volume, and intensity in each group).(iv)Report of ≤5% of serious adverse events.

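### Intensity fidelity is scored as failure ±1 repetition, a rule that does not fit the week 1, pain-limited and isometric work the protocol itself prescribes, so some compliant work counts as infidelity

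*Protocol article*

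**What the plan says.** **Scoring rule.** Protocol article, Primary feasibility outcomes, item (ii): "Exercise fidelity will be expressed as the percentage of the following key dose parameters", namely tempo, volume and "intensity [failure +/−1 repetition". No week or type of work is exempted. Under Videoconference exercise monitoring, fidelity is observed weekly for 12 weeks on the first set of each exercise.

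**Success criterion.** Data management and analysis, criterion (iii): "Achieving 66% or more of intervention fidelity (i.e. prescribed dose parameters including tempo, volume, and intensity in each group".

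**Prescribed departures from working to failure at the allocated load.**
- Plantarflexor six repetition maximum: "Week 1 exercise intensity will be adjusted down by 10% in both groups to minimise muscle soreness". In context this covers both load levels, hence all four arms.
- Exercise interventions, load progression text: when pain during exercise is five or more, "the load will be reduced so that pain severity is within an acceptable range". If pain remains unacceptable at minimal load, the exercise is done on flat ground.
- Same text: "Participants continuing to experience unacceptable pain will commence with isometric exercise", starting with five sets of 45 s.

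**Table 1.** For the whole 12 weeks it reads "Volitional muscular failure Yes Yes Yes Yes", without exception.

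**The concern.** A fidelity score should show whether participants did what the protocol asked. Here the protocol asks everyone for less load in week 1, and asks some participants for less load or for static holds later. The intensity component, however, still looks for a set that ends within one repetition of failure. A participant who follows instructions can lose the component.

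The criterion is applied arm by arm and informs whether a definitive trial is feasible. A low score could mean that participants did not follow the programme, or that pain kept them from the allocated dose. Those two explanations call for different redesigns, and a single score cannot tell them apart. Any downward shift would also be larger in whichever arm needs more pain-modified work.

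**Working it through.** The 66% threshold is a chosen figure with no derivation to reproduce. Two checks apply.

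**Step 1. Does the week 1 load miss failure ±1?** The only load-to-repetition relation in the protocol is that "the baseline eighteen RM load will be estimated from six RM using the following formula: 6RM × 0.65". So a load cut of 35% of the 6RM corresponds to 18 − 6 = 12 more repetitions.
- 6RM arms, linear: a 10% cut gives 10/35 × 12 = 3.4 repetitions in reserve.
- 18RM arms, linear: a 10% cut from 65% is 6.5 points, so 6.5/35 × 12 = 2.2.
- Log-linear, either load: ln(0.90)/ln(0.65) × 12 = 2.9.

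All lie outside one repetition. A cut of about 3% (6RM, 35/12 = 2.9%) to 4.5% (18RM, 2.9/0.65) already uses up the tolerance. A participant who stops at 6 or 18 therefore misses the intensity rule, and one who continues to failure exceeds the prescribed repetitions and misses volume. These are interpolations for the 6RM arms and extrapolations for the 18RM arms.

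For isometric holds no model is needed. They have no repetitions, no concentric and eccentric tempo, and five sets against the four in Table 1.

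**Step 2. What does this cost?** Inputs: 12 weekly observations and three parameters, so 36 component scores per participant. The article does not say how the parameters are combined, so the plausible rules are shown together.

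Week 1 alone, all else perfect:
- Mean of three parameters: 35/36 = 97.2%, a loss of 2.8 points.
- Intensity alone, or all three required: 11/12 = 91.7%, a loss of 8.3 points.

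Now add a fraction f of an arm on modified work for w of weeks 2 to 12. The maximum score is:
- A. Mean, only intensity affected: 1 − (1 + f·w)/36
- B. Mean, all three affected in modified weeks: 1 − (1 + 3·f·w)/36
- C. Intensity alone, or all three required: 1 − (1 + f·w)/12

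The documents give no f, w or level of compliance, so these are assumptions. With true compliance of 75%, taken as unrelated to modification, the recorded score is 0.75 × maximum:

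| f, w | A | B | C |
|---|---|---|---|
| week 1 only | 72.9% | 72.9% | 68.8% |
| 10%, 2 weeks | 72.5% | 71.7% | 67.5% |
| 20%, 4 weeks | 71.3% | 67.9% | 63.8% |
| 30%, 6 weeks | 69.2% | 61.7% | 57.5% |

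Worked line for 30% and 6 weeks, f·w = 1.8:
- A: 0.75 × (1 − 2.8/36) = 0.692
- B: 0.75 × (1 − 6.4/36) = 0.617
- C: 0.75 × (1 − 2.8/12) = 0.575

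**Step 3. How much modification would take a fully compliant arm of 12 below 66%?** Let m participants be modified throughout weeks 2 to 12.
- C: (12 − m) × 11/144 gives 68.8% at m = 3 and 61.1% at m = 4.
- B: 1 − (12 + 33m)/432 gives 66.7% at m = 4 and 59.0% at m = 5.
- A: 1 − (12 + 11m)/432 is still 66.7% at m = 12, so it never falls below the threshold.

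**The case against.** **The criterion already refers to the prescribed dose.** Scoring against the dose prescribed for that week is a natural reading of criterion (iii), and coding detail may sit in a fuller document that is not shown. This stands in part: how the parameters are combined is not a finding here. But the article does state a specific intensity rule and a specific threshold, and nothing in it says that adjusted weeks suspend the rule. Two careful analysts could score the same participant differently.

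**Week 1 below failure is an inference.** This stands as a limit. The 18RM is estimated rather than tested, a training tempo unlike the test tempo could bring failure earlier, and a pain-reduced load is not necessarily short of failure. Isometric holds do not depend on this inference.

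**A strict reading is defensible.** If pain prevents delivery of the allocated load and tempo, that is evidence against feasibility of the factorial contrast. Under adjusted-dose scoring alone, an arm doing nothing but isometric holds could score 100%. This stands, and it is why the fix needs both figures.

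**A reader might infer that compliant arms are likely to miss 66%, or that the week 1 reduction alone would cause it.** The documents do not support either. A participant affected only in week 1 scores 91.7% to 97.2% and helps the arm pass. Recorded values such as 63.8% or 57.5% require intensity to be scored alone or all three parameters to be required, whereas the article defines fidelity over three parameters. When these are averaged and only intensity is affected, every scenario in the table stays above 66%.

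**Conclusion.** The conflict is in the text: the failure ±1 rule has no exemption, and it cannot properly be applied to some of the work the protocol prescribes. Some compliant work is therefore scored as infidelity, and non-compliance is merged with dose intolerance in a per-arm success criterion.

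The numerical effect is modest unless modification is common. Week 1 costs at most 2.8 or 8.3 points. It could matter only for an arm already near the threshold, with true compliance below 0.66/(35/36) = 67.9% or 0.66/(11/12) = 72.0%. Larger effects need frequent pain-modified or isometric weeks, and their size depends on the aggregation rule: 69%, 62% or 57.5% in the heaviest scenario shown. That scenario rests on assumed values for compliance and modification. The point is worth correcting because the score is ambiguous in meaning, not because failure of the criterion is predicted.

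**What to change.** Reconcile the section on the six repetition maximum, Table 1, the load progression text, feasibility outcome (ii) and success criterion (iii), leaving every clinical rule as it is.

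1. Score compliance against the dose prescribed for that participant-week. Take week 1 out of the failure ±1 component, and score pain-limited or isometric weeks against the modified prescription.
2. Beside it, report by arm the proportion of participant-weeks delivered at the allocated RM and tempo, and the number of participants on pain-limited or isometric work.
3. State which of the two figures criterion (iii) uses.

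The cost is a scoring rule and one extra table. Weekly exercise load and weekly first-set observations are already to be collected. The downside is two fidelity figures in place of one.

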### Interventions

#### Exercise interventions

Participants will be asked to perform two unilateral isotonic exercises that load the ankle plantarflexor complex at a local gymnasium. Exercises include a standing straight knee calf raise and a seated bent knee calf raise. Both exercises will be performed on a Smith machine for both legs, irrespective of unilateral or bilateral symptoms (Fig. 2).

**Fig. 2 Fig2:**
[figure not shown]
Calf raises in a Smith machine. A1) Starting position; A2) Ending position from standing; B1) Starting position; B2) Ending position from seated

The study groups will vary in terms of load intensity and time-under-tension (Table 1). Four sets of each exercise will be performed three times per week for 12 weeks, with standardised rest times. Participants will be taught to perform the calf exercise with appropriate fidelity, including a full available range of plantar flexion and dorsiflexion, performing the movement in the sagittal plane, smoothly and with appropriate tempo. Exercises will be externally paced with a metronome (an application downloaded to participants’ phones) to ensure that participants achieve the target exercise tempo.

**Table 1 Tab1:** Calf exercise dosage for each group. RM repetition maximum; TUT time-under-tension; DF dorsiflexion; PF plantarflexion; min minutes; S seconds

	Group 1 High intensity with high time-under-tension	Group 2 High intensity with low time-under-tension	Group 3 Low intensity with high time-under-tension	Group 4 Low intensity with low time-under-tension
**Load intensity**	6 RM	6 RM	18 RM	18 RM
**Repetition**	6	6	18	18
**Sets**	4	4	4	4
**Frequency**	3×/week	3×/week	3×/week	3×/week
**Duration**	12 weeks	12 weeks	12 weeks	12 weeks
**Contraction time/rep**	3 s concentric 3 s eccentric	1 s concentric 1 s eccentric	3 s concentric 3 s eccentric	1 s concentric 1 s eccentric
**Rest in between reps**	No	No	No	No
**Rest in between sets**	2 min	2 min	2 min	2 min
**Contraction time per set**	36 s	12 s	108 s	36 s
**Total contraction time**	288 s	96 s	864 s	288 s
**Total loading time in session (with rests)**	16 min and 48 s	13 min and 36 s	19 min and 12 s	16 min and 48 s
**Volitional muscular failure**	Yes	Yes	Yes	Yes
**Range of motion**	0° to 15° DF 0° to 50° PF	0° to 15° DF 0° to 50° PF	0° to 15° DF 0° to 50° PF	0° to 15° DF 0° to 50° PF
**Time between sessions**	48 h	48 h	48 h	48 h
**Exercise form**	Seated and standing calf raising both performed on a Smith machine with barefoot	Seated and standing calf raising both performed on a Smith machine with barefoot	Seated and standing calf raising both performed on a Smith machine with barefoot	Seated and standing calf raising both performed on a Smith machine with barefoot

Exercise load progression will be monitored weekly based on the participant’s pain and ability. The load will be based on the volitional muscular failure, where failure is defined as an inability to do another full repetition. The load will be influenced by the self-reported pain during the exercise, with less than five on an eleven-point numerical rating scale (where zero is no pain and ten is the worst pain imaginable) being defined as acceptable [29]. For participants who report their pain as a five or more during the exercise, the load will be reduced so that pain severity is within an acceptable range. If the pain is still not acceptable with minimal load, bodyweight in standing and unloaded in seated, the exercise will be performed on flat ground. Participants continuing to experience unacceptable pain will commence with isometric exercise. As the dorsiflexed position is likely to be pain provocative due to greater Achilles tendon load, these will be performed with the ankle in a unilateral mid-range plantarflexed position, or bilateral if too painful. Initially, participants will perform five sets of 45 s at the highest load tolerable, based on pain and ability to complete the exercise, until isotonic exercise can be performed with acceptable pain response as assessed on a weekly basis (Fig. 3).

**Fig. 3 Fig3:**
[figure not shown]
Load progression over 12 weeks of rehab period. BW: Body weight

Exercise load will be monitored at baseline and during the intervention period by tendon loading testing (i.e. single-leg submaximal hop or single-leg calf raise). The single-leg submaximal hop will be performed with standardised instructions: participants will be asked to hop continuously, with hands on their hips. The magnitude of Achilles pain will be measured on Numerical Rating Scale (NRS) where zero (the lower limit) represents no pain and ten (the upper limit) represents the worst pain level [30, 31]. It will then be compared between the affected, or most affected, and non-affected side.

### Physical activity modification

All participants will receive standardised advice regarding physical activity modification based on a pain-monitoring model [14]. This approach has previously been used in Achilles tendinopathy and produces comparable outcomes to complete rest from physical activity [14]. They also will receive individualised advice about progressing their sports activity. Participants will be advised to continue walking, running and participating in sports activity if Achilles tendon pain during these activities is not beyond a five out of ten on an eleven-point NRS (where zero is no pain and ten is the worst pain imaginable) [14]. It is acceptable for pain after activity to increase if it returns to pre-baseline levels on a tendon loading test, either a single leg submaximal hop or single leg calf raise, within approximately 24 h.

For some people who may have been performing Achilles loading activities daily, it may be difficult to determine the 24-h response to load. Therefore, we also will be using pain with load tests to adjust physical activity. If the worst load test pain is greater than five with either the hop or calf raise, we will advise a reduction in the most intense stretch-shorten cycle Achilles loading activity the person will be undertaking; typically, this is running or sport, but can be walking. The reduction will be by 20–50%, depending on symptoms and reassessed weekly by the load tests. Once the worst load test pain is again less than five, participants will be advised to increase gradually.

